### 4.4 Sample size calculation

In order to estimate whether an ultra-low daily dose of artificial UVB (~0.5 SED) complying to the photobiological safety requirements for general lighting could be effective in raising serum 25(OH)D,

simulations based upon Diffey's model were conducted [42]. The simulation results indicate that when the foreseen intervention dose (0.45 SED) is applied in the optimal conditions (evenly over 8 hours and 20 minutes and 10.5 % body surface area exposure), a maintenance of summer serum vitamin D3 levels could be realized. Figure 2 represents the simulation (Exposure: 0.45 SED; Body Surface Area (BSA): 10.5%, front face (3.5%), 2 x back lower arms (3%), 2 x backside hand (3%), neck (1%)) as well as the effect of such an intervention in the foreseen study timespan of eight weeks. For the study it is expected that at optimized conditions a difference of about 17.6 nmol/L between intervention and control group can be realized in those 8 weeks. Having said that, the expected variance in actual exposure each day will be larger based upon the analysis of variations in exposure duration (desk occupancy) and body surface area exposure. The estimated impact of exposure to a minimum 0.225 SED and a body surface area % minimum of 6.5%) on serum vitamin D3 levels are depicted in Table 2.

[figure not shown]

**Figure 2:** Simulations results conducted to estimate the impact of a 8 week UVB exposure of office workers with input parameters (10.5% skin exposure: front face (3.5%), 2 x back lower arms (3%), 2 x backside hand (3%), neck (1%)). At start: 66.4 nmol/L; End intervention group: 61.7 nmol/L (- 4.7 nmol/L); End Control Group: 44.1 nmol/L (-22.3 nmol/L); Expected intervention effectiveness: +17.6 nmol/L. The UVB dose is evenly (UVI=0.06) given over a period of 8 hours and 20 minutes during the workday. This figure is based on exposure during 5 working days.

**Table 2:** Simulation results for expected serum vitamin D3 levels at reduced body surface area (BSA%) exposure and intervention dose (0.225 SED (50%)).

|                             |                                       | Estimated Serum VitD Intervention Effect (nmol/L) compared to control group |                      |                                              |

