A sample size calculation using Gpower was performed assuming that the intervention will reach a (conservative) difference of 8.8 nmol/L between the intervention and the control group (situation 3 in Table 2) at the final measurement point (at 8 weeks). This would mean that the decrease in the control group from baseline to week 8 would be -22.3 while in the intervention group this would be -13.5 (difference of 8.8 nmol/L). The sample size calculation is based on the statistical analysis conducted for the primary objective, namely the difference in serum 25(OH)D between the intervention and control group at the final measurement point, taking into account an alpha of 0.05 and a power of 0.90. The standard deviation within one group is estimated based on a previous similar study which also implemented low-dose UVB exposure to increase serum 25(OH)D in a sample of 20 healthy participants, albeit over a week period using three full-body UVB sunbed sessions [35]. In the post-measurement of this study, they found a significant increase in serum 25(OH)D of 13.9 nmol/L. One month after the end of the UVB intervention they still found a significant increase of 8.8 nmol/L, which is a similar difference we expect in the intervention group compared to the control group. The standard deviation for the power calculation was therefore based on the standard deviation on the difference score found in the sample in this study (similar sample size and similar changes in serum 25(OH)D), namely 8.4 nmol/L. The sample size for detecting a difference of 8.8 nmol/L assuming a standard deviation of 8.4 nmol/L in each group would be 17 participants in each group (see figure 3 below). As we currently only have the availability of 14 lamps, we will choose for 14 participants in each group, and aim to find a larger effect, which is not unlikely when on average, there is somewhat more than 50% desk occupancy and/or if we reach a higher exposure surface area.

[figure not shown]

**Figure 3.** Sample size calculation for change in serum 25(OH)D at 8 weeks

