## 7.2 Randomisation, blinding and treatment allocation

For a full visual overview of the allocation procedure see Figure 6. The independent agency CG selections will make a selection of eligible participants based in the in- and exclusion criteria (see sections 4.2 and 4.3). A list with eligible participants who are interested in participating in the study is mailed to the responsible researcher at the TU/e who will perform block randomization for assignment to the conditions. However, in case insufficient participants are available who work at least 2.5 days at their home office, selection for the intervention group will then be based on presence at the desk (at least 50%). This selection is believed not to influence the primary outcome parameter (25(OH)D serum levels) and as such the conclusions around the primary objective: Participants will not receive any (noteworthy, see [39]) UVB exposure (that could influence the serum 25(OH)D) unless they are allocated to the intervention group. In the statistical analysis, care will be taken to control for potential group differences in desk presence, time spent outside and vitamin D intake by food.

[figure not shown]

**Figure 6.** Allocation procedure

In addition to randomization, blinding is frequently applied to prevent that participants know they are in the control or intervention group. For this specific pilot, only 14 luminaires are available. These luminaires will be placed at the side of the participant's desk when allocated to the experimental group. As such the participant is aware that he or she will receive UVB. Blinding by reducing the sample size to 14 instead of 28 has been considered. However, to prevent that the data can be allocated (identified) to individual persons and to have sufficient power in the study, the total number of participants is estimated to be >25 in total. Since the 25(OH)D levels will not be affected by a pseudo-randomization and non-blinding strategy, it has been chosen to secure privacy of the participants and prioritize a sufficient sample size, and blinding is compromised.

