### 7.4.1.3 UV-dose measurements

Because the major determinant of artificial UV exposure will be time spent at desk each week and body surface exposed area, this will be recorded daily using a daily diary (see Figure 7), in which all subjects (also those in the control group) will self-report desk presence time and time spent outside in the morning and afternoon of their working day, and give an indication how much body surface areas was exposed during that day. Time spent outside during daylight in the weekend will also be reported on Monday.

Together with KNMI data we will be able to estimate the natural UVB exposure of the participant and provide for an analysis whether both groups behave similarly in their natural UVB dose. However, natural UVB exposure is expected to be minimal during the study months in autumn and winter (see [39])

Participants will gently be reminded to fill in the daily diary every day towards the end of the day. At the end of the week, they will receive a link to upload a scan or photo of the completed daily diaries or they can do this daily via a link provided at the start of the study.

|                                                  |               |              |               |              |               |              |               |              |               |              |
|--------------------------------------------------|---------------|--------------|---------------|--------------|---------------|--------------|---------------|--------------|---------------|--------------|
| Daily diary    week 1                            |               |              |               |              |               |              |               |              |               |              |
|                                                  |               |              |               |              |               |              |               |              |               |              |
| Estimated Desk Presence & Estimated Time Outside |               |              |               |              |               |              |               |              |               |              |
| Time/Day                                         | Monday        |              | Tuesday       |              | Wednesday     |              | Thursday      |              | Friday        |              |

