## 9. STATISTICAL ANALYSIS

The data analyses consist of multiple steps. All data will be presented quantitatively.

As a first step, we will inspect the distribution of the variables of interest. A Shapiro-Wilk test will be conducted to inspect normality of the variables. If needed and possible, a transformation of the scores will be performed to adhere to the assumption related to normality for the statistical analyses. Subsequently, an outlier detection will be performed with outliers determined as values more than 3 SD's from the mean.

Next, we will provide the descriptive statistics for the experimental and control condition for the variables measured only at baseline (see Table 1), as well as for the dependent variables (i.e., the variables for the primary (serum 25(OH)D) and exploratory research objectives (fatigue and sleep), see Section 2.) for each of the measurement points. Comparisons of the variables at baseline will be investigated via independent samples T-test to examine whether there were significant differences between the two groups for any of the variables at measured baseline. If the data appears to be not normally distributed and no transformation is applicable, we will employ a non-parametric test (Mann-Whitney test).

Subsequently, the main research objective (i.e., effects of the light intervention on serum 25(OH)D at week 8) will be investigated using an ANCOVA analyses with the intervention (yes/no) as predictor and change scores in serum 25(OH)D as outcome variable. This analysis will further be controlled for average desk presence and time spent outside. In case data is non-normally distributed a non-parametric test (Mann-Whitney test) will be conducted taking into account the limitation that this analysis cannot control for the mentioned confounders. Analyses will only be conducted with data from participants with both the baseline measurement and the final measurement point available. An alpha level of 0.05 will be used as criterion.

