- Your desk has been taped to indicate the area of sufficient user's UV-B exposure. Please, try to work as much as possible in this area to receive the intended safe dose of UVB irradiation.
- Please, indicate to others in the home office, not participating the test, to be placed at a minimal distance of 1.6m to the luminaire.
- Please, unpower the device if you experience skin redness or eye strain and please report the event.
- Any damage or unexpected behavior should be reported directly

Co-workers, not participating the test, should be placed at a minimal distance of 1.6m to the luminaire.

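### The primary ANCOVA adjusts for desk presence recorded after allocation, so its estimate departs from the effect of assigning the lamp whenever mean desk presence differs between arms

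*Protocol*

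**What the plan says.** Section 9 compares the change in serum 25(OH)D to week 8 by ANCOVA, with intervention (yes/no) as predictor, and adds: "This analysis will further be controlled for average desk presence and time spent outside". Its description of the non-parametric alternative calls these variables confounders. Section 7.2 gives the purpose: "care will be taken to control for potential group differences in desk presence, time spent outside and vitamin D intake by food".

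Other sections describe what desk presence is:

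- Section 7.4.1.3 has both groups report it in a daily diary during the study, and gives the reason: "Because the major determinant of artificial UV exposure will be time spent at desk each week and body surface exposed area".
- Section 9 calculates UVB dose for an exploratory mixed model from desk presence and clothing.
- Section 7.2 says nobody receives noteworthy UVB unless allocated to the lamp, and that allocation is not blinded.
- Section 12.2 tells lamp users, after mentioning the taped desk area: "Please, try to work as much as possible in this area to receive the intended safe dose of UVB irradiation".
- Sections 7.2, 7.4 and 10.2 allow a fallback. If too few people can guarantee 2.5 home-office days, those who can are assigned to the lamp first, in order of returned consent, and the rest become controls.

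**The concern.** A confounder is a cause of the outcome that differs between groups for reasons other than treatment. On-study desk presence does not fit. Under block randomisation it arises after assignment, and by the protocol's reasoning it affects 25(OH)D only through the lamp. Adjusting for it can credit part of the lamp's effect to the covariate. The slope should also exist in one arm only, whereas the stated model appears to fit one common slope.

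This is the only primary analysis, in a trial run with 14 per arm where Section 4.4 calculated 17. Section 4.4 accepts the shortfall partly because occupancy above 50% could give a larger effect. To the extent that lamp users exceed controls in occupancy, the covariate takes back part of that gain. The size and direction of the distortion would depend on behaviour after allocation, which would make a null result hard to interpret.

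**Working it through.** **The plan's own figure.** Section 4.4 plans with "assuming that the intervention will reach a (conservative) difference of 8.8 nmol/L between the intervention and the control group", SD 8.4 nmol/L, "taking into account an alpha of 0.05 and a power of 0.90". The standardised difference is 8.8/8.4 = 1.048. With the noncentral t distribution, a one-sided test needs 17 per group (power 0.911), which matches the protocol; a two-sided test needs 21. With 14 per group, power is 0.85 one-sided and 0.76 two-sided. Section 9 does not state sidedness ("An alpha level of 0.05 will be used as criterion"). Powers below are two-sided.

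**Dose model.** Section 4.4 expects that "a difference of about 17.6 nmol/L between intervention and control group can be realized in those 8 weeks" under optimal conditions. Table 2 gives 17.6 at 0.45 SED and 8.8 at 0.225 SED, both at 10.5% body surface. So take the effect as b × (fraction of lamp hours at the desk), with b = 17.6 in the lamp arm and 0 in controls.

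**What the adjusted coefficient estimates.** Let m1 and m0 be mean presence, and s1² and s0² the within-arm variances, in the lamp and control arms.

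- Effect of assignment: b·m1.
- Common slope: b·s1²/(s1² + s0²), which is b/2 when the spreads are equal.
- Adjusted effect: b·m1 − slope × (m1 − m0). With equal spreads this is b·(m1 + m0)/2.

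Example at 60% versus 50%: 17.6 × 0.60 = 10.56 without the covariate and 17.6 × 0.55 = 9.68 with it; 0.88/10.56 = 8% is removed.

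**Results.** Effects are from the formulas. Powers are from 20,000 simulated trials per row (14 per arm, residual SD 8.4). The presence means and their SD of 0.15 are assumptions; the protocol gives none.

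| Mean presence, lamp / control | Effect without → with covariate (nmol/L) | Change | Power without → with |
|---|---|---|---|
| 50% / 50% | 8.8 → 8.8 | 0 | 0.74 → 0.73 |
| 60% / 60% | 10.6 → 10.6 | 0 | 0.88 → 0.88 |
| 60% / 50% | 10.6 → 9.7 | −8% | 0.88 → 0.77 |
| 70% / 50% | 12.3 → 10.6 | −14% | 0.95 → 0.72 |
| 50% / 60% | 8.8 → 9.7 | +10% | 0.74 → 0.77 |
| 60% / 30% | 10.6 → 7.9 | −25% | 0.88 → 0.37 |

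Power at 50%/50% is a little below 0.76 because varying presence adds variance in the lamp arm.

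**Fallback allocation, extreme case.** Suppose presence is uniform on 50–100% in the lamp arm and 0–50% in controls.

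- Without the covariate: 17.6 × 0.75 = 13.2.
- With it: 17.6 × (0.75 + 0.25)/2 = 8.8, a loss of 4.4/13.2 = 33%.
- Within-arm variance of presence is 0.5²/12 = 0.0208, and between-arm variance is (0.5/2)² = 0.0625.
- R² between arm and presence is 0.0625/0.0833 = 0.75. The variance inflation factor is 1/(1 − 0.75) = 4, so the standard error doubles, from about 3.2 to about 6.6.
- Power falls from about 0.97 to about 0.25.

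**Fallback with surplus qualifiers as controls.**

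- If 4 of 14 controls are in the 50–100% range: m0 = (4 × 0.75 + 10 × 0.25)/14 = 0.393 and s0² = 0.0208 + 0.25 × (4/14) × (10/14) = 0.0718. The slope is 17.6 × 0.0208/(0.0208 + 0.0718) = 3.96. The adjusted effect is 13.2 − 3.96 × 0.357 = 11.8 (−11%), with a standard error of about 4.2 and power of about 0.76.
- If 7 of 14 are: m0 = 0.50, s0² = 0.0833, slope 3.52. The adjusted effect is 13.2 − 3.52 × 0.25 = 12.3 (−7%), with power of about 0.88.

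**The case against.** The strongest reply is that block randomisation is the main plan and Section 4.2 requires at least 2.5 desk days of everyone. With presence uniform on 50–100% in both arms, the effect is 13.2 with or without the covariate, and power is about 0.97 either way. That stands: nothing is lost in expectation when mean presence is equal.

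A reader might infer from Section 12.2 that lamp users are told to sit longer. The sentence follows the remark about the taped area, so it can equally mean where to sit, and Section 5 asks everyone to carry on working as usual. An effect of assignment on desk hours is possible in an unblinded trial, but it is not clearly instructed.

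A reader might also equate desk presence with the dose. Sections 7.4.1.3 and 9 include exposed skin, and in Table 2 body surface alone moves the 8-week effect from 17.6 to 13.6.

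The steepest fallback figures need every control to be below 50% presence. Surplus qualifiers who become controls reduce the loss considerably.

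Finally, the exploratory intervention mixed model in Section 9 does not list desk presence as a covariate, so an estimate without it should appear. This softens the consequence, but that model is exploratory and the primary test remains the adjusted one.

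What survives is that the covariate is mislabelled as a confounder, has a one-arm slope fitted as common, gains nothing when the arms are balanced and distorts the estimate when they are not.

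**Conclusion.** The adjustment for on-study desk presence is wrong as written, and its harm is conditional. Its expected effect on the estimate is zero with equal mean presence. It removes about 8% to 14% if lamp users sit 10 to 20 percentage points more than controls at 50%, and adds about 10% if controls sit 10 points more. Under the fallback, the loss ranges from about 7% with many surplus qualifiers among the controls to about one third, with a doubled standard error, when there are none.

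The documents do not support saying that the model always removes part of the effect, or that the primary test will fail. The figures rest on an effect linear in desk time, which Table 2 supports at 10.5% body surface (its 6.5% rows, 13.6 and 5.5, are not proportional), on no effect of desk presence in controls, and on assumed presence distributions.

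Time outside is a lesser matter. It is also recorded after allocation, but it is a separate UVB source that Section 7.4.1.3 expects to be minimal in these months, and no calculation here shows harm from keeping it.

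**What to change.** In Section 9, remove on-study average desk presence from the primary ANCOVA and stop calling it a confounder. Adjust for variables fixed before the lamp is installed: baseline 25(OH)D and, optionally, the baseline vitamin D food intake already collected at week 0 (Section 7.4.1.2). If the fallback allocation is used, add desk presence reported before allocation, because the arms would then differ by selection and dropping the covariate alone would leave that unadjusted.

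Keep on-study desk presence in the exploratory dose mixed model, and report the primary model adjusted for it only as a sensitivity analysis. Align Section 7.2 with this. Time outside may stay or go; the choice should be stated.

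The cost is a wording change in Sections 7.2 and 9. The fallback covariate needs one more screening item, expected desk days recorded as a number, since Section 7.3.2 asks candidates only to confirm that they meet the criteria.

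### A normality pretest on the variables chooses the primary analysis, and one branch is an unadjusted Mann-Whitney test with neither confounder control nor a planned estimate in nmol/L

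*Protocol*

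**What the plan says.** All of the rule is in Protocol Section 9.

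- First step: "A Shapiro-Wilk test will be conducted to inspect normality of the variables".
- Second step: "If needed and possible, a transformation of the scores will be performed to adhere to the assumption related to normality for the statistical analyses". The type of transformation is not named. Outlier detection at 3 SD follows.
- Primary analysis: "using an ANCOVA analyses with the intervention (yes/no) as predictor and change scores in serum 25(OH)D as outcome variable", and "This analysis will further be controlled for average desk presence and time spent outside". Baseline 25(OH)D is not listed as a covariate here. It appears only in the exploratory mixed model.
- Fallback: "In case data is non-normally distributed a non-parametric test (Mann-Whitney test) will be conducted taking into account the limitation that this analysis cannot control" for those confounders. Shapiro-Wilk is the only normality criterion in the section.

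Two other places bear on this. Sections 7.2, 7.4 and 10.2 allow non-random assignment: if too few people can guarantee the required home-office days, those who can go to the intervention group first and the others become controls. For this case Section 7.2 promises that "care will be taken to control for potential group differences in desk presence, time spent outside and vitamin D intake by food". Section 2.1 asks how far the light sustains summer 25(OH)D levels, and Section 4.4 plans for a difference of 8.8 nmol/L, so the trial wants a size as well as a p-value.

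**The concern.** The method for the primary endpoint is chosen by the same data that it then tests. The criterion is also misplaced. ANCOVA needs approximate normality of its residuals, not of the raw variables and not of the covariates. A real group difference, or a skewed covariate such as time outside, can make a variable look non-normal while the model is sound.

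The branches do not answer the same question. ANCOVA gives an adjusted mean difference in nmol/L. A transformed ANCOVA gives a difference on another scale. Mann-Whitney gives an unadjusted rank comparison, and no accompanying estimate is specified. The protocol admits that the last branch loses confounder control, yet Section 7.2 names that control as its answer to group differences when allocation is not random. The safeguard could therefore disappear in the situation for which it was written.

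**Working it through.** **The plan's own figure.** Section 4.4 gives 17 per group for a difference of 8.8 nmol/L, SD 8.4, alpha 0.05 and power 0.90. The standardised difference is 8.8/8.4 = 1.048. A noncentral-t calculation gives 17 per group at one-sided 0.05 (power 0.911) and 21 at two-sided 0.05 (power 0.842 with 17). The figure is thus reproduced one-sided; the text does not state the sidedness. With the 14 per group actually planned, unadjusted power is 0.854 one-sided and 0.761 two-sided. Nothing below depends on this.

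**Simulation.** From the documents: 14 vs 14, SD 8.4, effect 0 or 8.8 nmol/L, ANCOVA with two covariates. Assumed: two-sided 0.05; Shapiro-Wilk at 0.05; time outside explains a share R² of the within-group variance; desk presence is not prognostic; errors are normal, gamma (shape 4 or 2) or t with 5 df. The model is

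change = −22.3 + effect × group + 8.4 × (√R² × outside + √(1−R²) × error).

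The two-stage rule uses Mann-Whitney if Shapiro-Wilk on the pooled changes gives p < 0.05, and ANCOVA otherwise. The transformation step is not simulated. There were 4,000 runs per scenario.

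**1. How often the method switches (balanced groups).** With normal errors, 4–5% if changes are pooled and 9–10% if either group can trigger it. With the skewed or heavy-tailed errors, 10–72% pooled and 19–59% by group. In a separate check, a single value at 3 to 3.5 SD raised the pooled rate from about 4% to 8–16%.

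**2. Balanced groups.**

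| | ANCOVA | Mann-Whitney | Two-stage |
|---|---|---|---|
| Type I error, all scenarios | 0.044–0.054 | 0.043–0.051 | 0.044–0.054 |
| Power, R² = 0 | 0.706–0.741 | 0.708–0.827 | 0.707–0.791 |
| Power, R² = 0.3 | 0.855–0.869 | 0.716–0.779 | 0.852–0.863 |

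Against always using ANCOVA, the two-stage rule costs at most 0.866 − 0.852 = 0.014 in power (gamma shape 4, R² = 0.3) and gains up to 0.791 − 0.737 = 0.054 (gamma shape 2, R² = 0).

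**3. Does the choice matter to the conclusion?** With a true effect of 8.8, ANCOVA and Mann-Whitney fall on opposite sides of p = 0.05 in 10–14% of trials at R² = 0 and 17–19% at R² = 0.3. This counts all trials; the share in which the switch also fires is smaller.

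**4. Groups unequal on a prognostic covariate, true effect 0.** More time outside in the intervention group:

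| Imbalance, R² | Errors | ANCOVA | Mann-Whitney | Two-stage |
|---|---|---|---|---|
| 0.5 SD, 0.1 | normal | 0.052 | 0.057 | 0.052 |
| 0.5 SD, 0.1 | gamma 2 | 0.048 | 0.069 | 0.057 |
| 0.5 SD, 0.3 | normal | 0.050 | 0.099 | 0.051 |
| 0.5 SD, 0.3 | gamma 2 | 0.052 | 0.108 | 0.065 |
| 0.75 SD, 0.1 | normal | 0.049 | 0.086 | 0.051 |
| 0.75 SD, 0.1 | gamma 2 | 0.047 | 0.100 | 0.074 |
| 0.75 SD, 0.3 | normal | 0.048 | 0.165 | 0.054 |
| 0.75 SD, 0.3 | gamma 2 | 0.049 | 0.176 | 0.073 |

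A repeat of the 0.75 SD, R² = 0.3 case with 10,000 runs gave 0.158 (normal) and 0.183 (gamma 2) for Mann-Whitney, 0.056 and 0.080 for the two-stage rule, and 0.050 and 0.051 for ANCOVA. Here ANCOVA has the advantage that the imbalanced covariate is measured without error and modelled correctly.

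**The case against.** The fallback is prespecified, its cost is admitted in the same sentence, and this is a self-described pilot. The test level and the exact quantity tested could stand in a statistical analysis plan, so their absence is not held against the protocol. The protocol also expects its covariates to be weak: Section 7.2 says that participants get no noteworthy UVB outside the intervention, and Section 7.4.1.3 expects natural UVB to be minimal. The confounding harm needs the contingent allocation route or chance imbalance, together with a prognostic covariate. All of this stands, and it limits the size of the point.

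A reader might infer four stronger things that the documents do not support.

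- *That the switch drops baseline adjustment.* The planned ANCOVA lists no baseline covariate, so there is none to lose.
- *That negative expected changes (−22.3 and −13.5) force the rule to Mann-Whitney.* Serum 25(OH)D is positive and can be logged before differencing. That is a third branch, though it also leaves the nmol/L scale.
- *That Mann-Whitney has less power in general.* Among trials in which the pretest fires, its power was 0.85 against 0.70 for ANCOVA (gamma 2, R² = 0) and 0.80 against 0.67 (t with 5 df, R² = 0). It lost with normal errors at R² = 0.3 (0.63 against 0.80), and by 3–4 points with non-normal errors at R² = 0.3.
- *That all information in nmol/L is lost.* Section 9 still reports group descriptives at each visit and an exploratory mixed model. What is missing in this branch is a primary between-group estimate on that scale.

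**Conclusion.** The point holds in a limited form. The rule makes the primary analysis depend on the data through a test of the wrong quantity, and one of its three outcomes has no confounder control and no planned effect estimate in nmol/L. Under balanced randomisation it neither inflates type I error nor costs power in general.

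The numerical harm appears when groups differ on a prognostic covariate, which non-random allocation makes more plausible. At an assumed 0.75 SD imbalance and R² of 0.3, type I error is about 0.16–0.18 if Mann-Whitney is used and about 0.05–0.08 for the rule as a whole, against about 0.05 for ANCOVA. At 0.5 SD and R² of 0.1, the rule as a whole gives 0.052–0.057. Imbalance, R² and error shape are assumptions; the documents give none of them. In the balanced scenarios ANCOVA held its level at 0.044–0.054 even with skewed and heavy-tailed errors at 14 per group, so the switch protects against little.

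**What to change.** In Section 9:

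1. Name one covariate-adjusted ANCOVA of the week-8 change, on the nmol/L scale, as the primary analysis whatever Shapiro-Wilk shows, and report the adjusted difference with its confidence interval.
2. Check the model residuals, not the raw variables.
3. If residuals are clearly non-normal, keep the same adjusted coefficient and use permutation or robust inference for it.
4. Report Mann-Whitney, and any transformed analysis, only as sensitivity analyses.

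The cost is a few sentences and a few lines of code; the sample size does not change. There is one small downside: if errors are strongly skewed or heavy-tailed and the covariates are weak, some power is given up, at most about 5 points against the two-stage rule in the scenarios above.
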